### Power and sample size

We have powered our study to detect an 0.5 SD effect size for the primary outcome. This will also detect the same effect size for secondary outcomes. Our pilot data identified a likely effect size of 1.7 kg/m^2 ^reduction in BMI. This is equivalent to 0.6 SD given evidence from our pilot study and from other interventions [18] that the SD of change in adolescent BMI is approximately 2.0 kg/m^2^. Lifestyle modification programmes in obese children result in improvements in HR-QOL of 0.3-0.5 SD [33,34].

Sample size: 126 subjects is sufficient to detect an effect size of 0.5 at 80% power and 5% significance. This sample will be inflated to account for the clustering due to any persistent therapist effects [35]. Using a therapist cluster size (C) of 10 subjects and an assuming an ICC of 0.025, we will require an inflation of our existing sample size to (1226 × (1 + (C-1)*0.025)) = 155. We will recruit 200 subjects to allow for 20% drop-out.

### Statistical analysis

Main analysis of primary outcome: Analyses will be undertaken by the programme statistician, supervised by [name]. An intention to treat analysis will be undertaken for the primary outcome. A linear regression model that accounts for clustering effects will be fitted. The main analysis will incorporate correction for missing data. The model can either be fitted using an EM algorithm or MCMC approach. This analysis will be performed adjusted for baseline BMI, age and sex. The biases caused by missing 3 and 6 months outcome data will be addressed through multiple imputation by methods that utilise the number of attempts to achieve response [36] as well as other sensitivity analyses for informative missingness [37]. We will undertake a complier average causal effect (CACE) analysis to identify the difference in mean outcome amongst compliers. CACE recognizes the initial randomization and thus overcomes the problems faced by per-protocol and on-treatment analyses.

Secondary analyses of primary outcome:

a. The main analysis will be repeated without correction for missing data, e.g. using complete cases analysis (intention to treat), adjusted for baseline BMI, age and sex.

b. Complier average causal effect (CACE) analysis to identify the difference in mean outcome amongst compliers, accounting for missing data, adjusted for baseline BMI, age and sex.

c. CACE analysis without correction for missing data, adjusted for baseline BMI, age and sex.

d. Sensitivity analyses for informative missingness.

In this study, compliance for the intervention arm is defined as fulfilling the following criteria: 1) attendance to session one, 2) attendance to at least one session in each of the four modules of the intervention, and 3) attendance to a minimum of eight of the twelve sessions in total. Participants in the intervention arm failing to fulfil one or more of these criteria are classified as non-compliers.

Main analysis of secondary outcomes:

In addition to secondary outcomes listed above, BMI at 6 months after end of intervention (Week 52) is included as a secondary outcome. Similarly to the primary outcome analyses, an intention to treat analysis will be applied. A linear or logistic regression model that accounts for clustering effects will be fitted for continuous and binary outcomes, respectively. For ordinal outcomes, such as LIKERT scale outcomes, an ordinal logistic regression model will be fitted. The main analysis will incorporate correction for missing data.

Secondary analyses of secondary outcomes:

a. The main analysis will be repeated without correction for missing data, e.g. using complete cases analysis (intention to treat), adjusted for baseline BMI, age and sex.

b. CACE analysis to identify the difference in mean outcome amongst compliers, accounting for missing data, adjusted for baseline BMI, age and sex.

c. CACE analysis without correction for missing data, adjusted for baseline BMI, age and sex.

Software: Depending on the choice of implementation, standard software for generalised linear models, e.g. STATA (to implement EM algorithm) or WinBUGS (to implement MCMC) will be used for the main analyses.

Reporting of the statistical analyses will follow CONSORT guidelines.

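### The only covariates written for secondary outcomes are baseline BMI, age and sex; apart from Week 52 BMI, continuous outcomes lose precision by omitting their own Week 0 value

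*Protocol article*

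**What the plan says.** All references are to the protocol article.

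- **Primary outcome** (Statistical analysis): "This analysis will be performed adjusted for baseline BMI, age and sex". Baseline BMI is here the outcome's own baseline.
- **Secondary outcomes, main analysis:** "Similarly to the primary outcome analyses, an intention to treat analysis will be applied", and "A linear or logistic regression model that accounts for clustering effects will be fitted for continuous and binary outcomes, respectively", with an ordinal model for ordinal outcomes. No covariates are named.
- **Secondary outcomes, secondary analyses:** item a repeats the main analysis "without correction for missing data, e.g. using complete cases analysis (intention to treat), adjusted for baseline BMI, age and sex". Item b is a "CACE analysis to identify the difference in mean outcome amongst compliers, accounting for missing data, adjusted for baseline BMI, age and sex". Item c is a "CACE analysis without correction for missing data, adjusted for baseline BMI, age and sex".
- **Data collected** (Assessment, Table 2): anthropometry, quality of life, blood pressure, venepuncture and psychological function all have a Week 0 measurement.
- **Power and sample size:** of the 0.5 SD target it says "This will also detect the same effect size for secondary outcomes", and then "Lifestyle modification programmes in obese children result in improvements in HR-QOL of 0.3-0.5 SD".

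**The concern.** The covariate list for the secondary outcomes matches that for the primary outcome word for word and appears to have been carried over. For BMI it contains the covariate that usually does most to reduce residual variance, the baseline of the outcome itself. For PedsQL, IWQOL-Kids, the Eating Attitudes Test, self-esteem, waist, fat mass, blood pressure, lipids and insulin/HOMA it does not, and baseline BMI may be a weak substitute for, say, a baseline quality-of-life score.

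These outcomes carry the trial's secondary hypothesis, and quality of life is also to be explored as an intermediate step towards BMI change (Abstract). Minimisation balances on sex alone (Randomisation), so the design does nothing to limit chance differences in baseline quality of life, psychological scores or bloods. The analysis model is where they would be dealt with. Precision also matters because the cited quality-of-life effects run from 0.3 SD upwards, while the trial is sized for 0.5 SD.

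**Working it through.** **1. The plan's own figure.** With a 0.5 SD effect, 80% power and 5% significance (two-sided assumed), n per arm = 2 × (1.960 + 0.842)² / 0.5² = 62.8, rounded up to 63, so 126 in total, as stated. The design effect is 1 + (10 − 1) × 0.025 = 1.225, and 126 × 1.225 = 154.35, rounded up to 155, as stated. (The 1226 printed in the formula must be a slip for 126, since 155 follows only from 126.) Allowing for 20% drop-out, 155 / 0.8 = 193.75, so 194 against 200 recruited. The calculation uses no covariate gain.

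**2. Effective size for the comparison.** 155 / 1.225 = 126.5 independent participants, or 63.3 per arm.

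**3. Effect of a covariate.** In a linear model, a covariate with correlation r with the outcome leaves residual variance 1 − r² (outcome SD set to 1). Power is Φ( d / [√(1 − r²) × √(2/63.3)] − 1.960 ), with √(2/63.3) = 0.178. For example, d = 0.3 and r = 0.5 give a standard error of 0.866 × 0.178 = 0.154, then 0.3 / 0.154 = 1.948, and Φ(−0.012) = 0.495.

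| r with outcome | 1 − r² | Power, 0.3 SD | Power, 0.5 SD |
|---|---|---|---|
| 0 | 1.00 | 39.3% | 80.3% |
| 0.3 | 0.91 | 42.4% | 83.8% |
| 0.5 | 0.75 | 49.5% | 90.1% |
| 0.6 | 0.64 | 55.9% | 94.0% |
| 0.7 | 0.51 | 65.6% | 97.6% |
| 0.8 | 0.36 | 80.3% | 99.7% |

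**4. The comparison that matters.** The written model is not unadjusted, because it contains baseline BMI. The documents give no correlations, so two ranges are assumed: 0 to 0.3 between baseline BMI and the outcome, and 0.5 to 0.7 between the outcome's own baseline and its follow-up value. Then:

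- The own-baseline model has between 0.51 / 1.00 = 51% and 0.75 / 0.91 = 82% of the residual variance of the BMI-adjusted model.
- Power at 0.3 SD is about 50-66% instead of about 39-42%.
- Power at 0.5 SD is about 90-98% instead of about 80-84%.
- If both correlations are 0.3, the two models have the same residual variance and there is no gain.

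The contribution of age and sex is ignored on both sides. The effect size is taken in units of the outcome's SD.

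**The case against.** The strongest reply is that the main analysis of the secondary outcomes names no covariates at all. The reference to the primary analysis is attached to the intention-to-treat principle, and no sentence excludes an own-baseline term. Per-outcome covariate lists are commonly left to a statistical analysis plan, which is not shown here. This stands in part: for the main analysis the set is implied, not stated. The implication is nevertheless strong, because item a presents itself as the main analysis repeated with different handling of missing data. For the complete-case and both CACE analyses the set is explicit. The point therefore rests on a choice that is written down, not on silence.

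Four further limits stand:

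- For BMI at Week 52, baseline BMI is the outcome's own baseline, so nothing is lost there.
- The size of the gain depends wholly on assumed correlations. For waist and fat mass, baseline BMI may correlate more strongly than the 0.3 used here, and the gain would then be smaller.
- The 1 − r² factor applies to linear models. For binary or ordinal outcomes the gain is different and not calculated. DAWBA diagnoses may carry little information at baseline, because young people with significant mental health problems are excluded. For accelerometry an own baseline is uncertain: the Outcomes section describes a single recording per participant, while Table 2 shows three time points.
- Even with own-baseline adjustment, power at 0.3 SD stays below 80% over the assumed range. The shortfall there comes mainly from sample size.

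**Conclusion.** The point holds as a matter of precision. For continuous secondary outcomes other than Week 52 BMI, the only covariate set written down leaves out a baseline value that the trial collects. With the assumed correlations (own baseline 0.5 to 0.7, baseline BMI 0 to 0.3), this costs roughly 7 to 26 percentage points of power at 0.3 SD (49.5 − 42.4 = 7.1; 65.6 − 39.3 = 26.3). The cost is nil if both correlations are 0.3.

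A reader might infer more than the documents support:

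- **Biased treatment estimates.** Allocation is randomised, so omitting the own baseline does not bias the comparison on average. Chance imbalance in the baseline goes uncorrected, but it is part of the same sampling variance already counted in the power figures and should not be added as a second cost.
- **An invalid sample size.** The 0.5 SD calculation reproduces without any covariate gain and is unaffected. The article claims power for secondary outcomes only at that effect size.
- **Deliberate exclusion of the own baseline from every analysis.** The text does not say this, and Week 52 BMI is a counterexample to any claim about all secondary outcomes.

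**What to change.** State the covariates for the secondary outcomes explicitly, for the main analysis as well as items a to c. For each continuous secondary outcome measured at Week 0, adjust the main, complete-case and CACE analyses for that outcome's own baseline value, age and sex, keeping baseline BMI if wished. Include the same baseline value in the imputation model. For binary and ordinal outcomes, do the same where a baseline is available and informative.

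This is one or two sentences in the analysis section. It needs no new data and costs one degree of freedom per model. Fixing it in advance also removes any choice of covariates made with results in view.

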### Economic evaluation

The economic evaluation will be conducted from the public services (NHS, education, personal and social services) perspective in the primary analysis, and from the societal prospective in a sensitivity analysis.

The primary effectiveness outcome will be quality adjusted life years (QALYs) measured over a time horizon of 1 year based on EQ-5D scores collected during the trial; secondary analysis will examine the IWQoL to inform non preference-based cost-effectiveness analyses. The following cost components will be included in the analysis: weight-related inpatient and outpatient hospital, primary care and child and adolescent mental health services contacts; any other NHS treatments, or treatment paid for by the PCT, received to support weight loss; the cost of additional support provided at school; benefit receipt, family and social fund support, and the receipt of direct payments from social services or registered charities; and the impact of child care on parents' ability to work. Cost-effectiveness will be measured based on the incremental cost per QALY gained of the intervention versus the control. We shall use non-parametric bootstrap estimation to derive 95% confidence intervals for mean cost and effect differences between the trial groups and to calculate 95% confidence intervals around the incremental cost effectiveness ratios.

A series of univariate, multi-way and probabilistic sensitivity analyses will be undertaken to explore the implications of uncertainty on the incremental cost-effectiveness ratios and to consider the broader issue of the generalisability of the study results. The sensitivity analyses will include extending the baseline cost-effectiveness model to a life-time time horizon using Markov modelling. We will construct cost-effectiveness acceptability curves constructed using the net benefits approach.

### Trial Status

The HELP study is a 51 month study.

The Set-up phase took place in Months 1-6. The providers were recruited and trained to deliver the intervention and control arms in M 6-9. Recruitment of young people commenced in M9 and will continue till M33. Baseline assessments commenced in M12 and will continue for 2 years till M36. Subjects were randomised in M12, and delivery of intervention and control arms will run from M12 to M 42. Final data collection will occur M18 to 42. Database completion, analysis and writing up will occupy M45-51.
